##### Sample size and power calculations

The study is powered to detect a clinically meaningful difference in adherence to HCC surveillance. With four sites and a minimum of 10 participants per site (total n=40), the study will have 80% power to detect an absolute difference of 24 percentage points in adherence between the control and On-Country surveillance periods (eg, an increase from 10% in the control periods to 34% in the intervention periods). This calculation is based on a two-sided alpha of 0.05 and assumes four measurement periods over 24 months (one during the initial baseline control period for all sites, followed by three 6-monthly measures). It further assumes an intra-class correlation coefficient of 0.05 to account for the correlation between participants within the same site. To ensure a final analytic sample of at least 40 participants, we will recruit 45 individuals to allow for a potential attrition rate of approximately 10%.^42^ The overall 24% difference in adherence between care types is a conservative estimate of anticipated improvement, based on our published experience of 64% improvement in 2-year surveillance following a clinical practice improvement programme in a metropolitan hospital setting (44). The estimated 10% adherence in the control period is also conservative given much lower values described in current literature.^43^

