### Primary outcome

The primary analysis will be conducted on a modified intention-to-treat (ITT) basis, where all participants that are randomised are included in the analysis and are assigned to their original treatment according to the randomised crossover schedule, regardless of treatment received. Adherence to HCC surveillance will be operationally defined as a binary variable and recorded for each participant during each 6-month (±2 months) study period. A participant will be considered 'adherent’ (coded as 1) if they complete both a liver ultrasound and the required serum biomarker tests within that period; otherwise, they will be 'non-adherent’ (coded as 0). Analysis of the binary adherence outcome will be performed using a generalised linear mixed-effects model (GLMM) with a logit link function. The model will include fixed effects for the treatment (usual care vs On-Country), time (as a 6-month categorical variable) and time x treatment. To account for the clustered data structure, random intercepts for site and for participant (to account for repeated measures on individuals and for repeated measures within each site). The primary intervention effect will be reported as the estimated marginal mean difference in proportions (95% CI) for On-Country versus usual care surveillance. We will also report the odds ratio (95% CI) for adherence for On-Country versus usual care surveillance. Missing outcome data will be investigated for patterns, and, if assumed to be missing at random, we will conduct a sensitivity analysis using a GLMM with multiply imputed datasets to ensure our findings remain robust. Subgroup analyses by site, gender, age and liver aetiology will be conducted depending on the final number of participants recruited.

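### The stated missing-data sensitivity analysis assumes missing at random, as a likelihood-fitted primary model already does, so it does not test departures from that assumption

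*Protocol article*

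**What the plan says.** Under Data analysis, Primary outcome, the primary model is a "generalised linear mixed-effects model (GLMM) with a logit link function". It has "fixed effects for the treatment (usual care vs On-Country), time (as a 6-month categorical variable) and time x treatment", plus random intercepts for site and participant. The analysis is modified intention-to-treat, in which "all participants that are randomised are included in the analysis". A participant counts as adherent in a 6-month period "if they complete both a liver ultrasound and the required serum biomarker tests within that period"; every other case is coded 0.

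For missing outcomes, patterns are to be examined and then "if assumed to be missing at random, we will conduct a sensitivity analysis using a GLMM with multiply imputed datasets". The purpose given for this check is "to ensure our findings remain robust". The article states no other missing-data analysis and names no variables for the imputation model. It does not say what follows if MAR is not assumed, or which person-periods count as missing rather than 0.

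Under Sample size and power calculations, the target effect is "an increase from 10% in the control periods to 34% in the intervention periods", and "we will recruit 45 individuals to allow for a potential attrition rate of approximately 10" per cent. Under Quantitative data, age, sex, medical history, blood results and fibrosis scores are collected before randomisation. None of these is listed as a term in the primary model.

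**The concern.** A sensitivity analysis should change the assumption in doubt. A likelihood-fitted mixed model is valid when outcomes are MAR given its terms. Imputing under MAR from the same information and refitting the same kind of model keeps that assumption, so the two results should agree whether or not it is true.

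The trigger adds to the problem. The check is tied to MAR being assumed, and examining observed patterns cannot establish MAR. If MAR is doubted, the article gives no analysis, although that is when one is most useful.

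The design gives this some weight. Every site starts in usual care and ends On-Country, so exits that accumulate over time fall mainly in On-Country periods. An effect that depends on how those exits are handled could pass the stated check unchanged.

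**Working it through.** **Inputs.** From the article: 10% and 34% adherence (24 points), about 10% attrition, four periods, four sites, a switch after 6 to 18 months of usual care, and 80% power at two-sided 0.05. Assumed here: all attrition becomes missing outcome data; cumulative loss is 3.3%, 6.7% and 10% in periods 2, 3 and 4; observed adherence is 10% and 34% in every period; sites switch at 6, 12 or 18 months with one time shared by two sites (the randomisation figure is not available). The results are crude averages by condition, without the model's time adjustment.

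**1. The plan's own figure.** 40 / (1 − 0.10) = 44.4, rounded up to 45. This matches.

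**2. Do the two analyses share a bias?** Take a case that is not MAR. True adherence is 10% and 34%. Usual-care records are missing at random (10%). On-Country records are missing with probability 0.02 if adherent and 0.141 if not.

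- On-Country share missing: 0.34 × 0.02 + 0.66 × 0.141 = 0.100.
- Observed On-Country adherence: 0.34 × 0.98 / (0.34 × 0.98 + 0.66 × 0.859) = 0.3332 / 0.9001 = 37.0%.
- Available-case difference: 37.0 − 10.0 = 27.0 points, against a true 24.0.

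A simulation of this case (80 independent records per condition, 20 imputations, 4,000 runs, simple proportions rather than the full mixed model) gave 27.0 points for available cases and 27.0 for imputation under MAR. The SD of their difference was 0.5 points. They agree, and both are 3 points too high. Setting missing to non-adherent gives 0.34 × 0.98 − 0.10 × 0.90 = 24.3 points; it lands near the truth because of the mechanism chosen.

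**3. How far could the effect move?** Let m1 and m0 be the missing shares in On-Country and usual-care periods.

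- Missing set to non-adherent: 34(1 − m1) − 10(1 − m0).
- Lower extreme (missing On-Country all 0, missing usual care all 1): subtract 100·m0 from that.
- Upper extreme (the reverse): add 100·m1 to it.

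For switches at 6, 6, 12 and 18 months there are 9 On-Country site-periods, with missing percentages summing to 20 + 20 + 16.7 + 10 = 66.7. There are 7 usual-care site-periods, summing to 0 + 0 + 3.3 + 10 = 13.3. The other rows follow the same way.

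| Switch times (months) | m1 | m0 | Missing = non-adherent | Lower | Upper |
|---|---|---|---|---|---|
| 6, 6, 12, 18 | 66.7/9 = 7.4% | 13.3/7 = 1.9% | 21.7 | 19.8 | 29.1 |
| 6, 12, 12, 18 | 63.3/8 = 7.9% | 16.7/8 = 2.1% | 21.5 | 19.4 | 29.4 |
| 6, 12, 18, 18 | 56.7/7 = 8.1% | 23.3/9 = 2.6% | 21.5 | 18.9 | 29.6 |

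**4. Against the planned precision.** Taking the stated power at face value, the standard error is about 24 / (1.96 + 0.84) = 8.6 points, so significance needs about 1.96 × 8.6 = 16.8 points. The lowest extreme, 18.9, is still above this. With usual care at 10% and the standard error held fixed, an observed effect d falls to about 0.926d − 2.5 (first row) or 0.919d − 3.1 (last row) at the lower extreme. These reach 16.8 at d = 20.8 and d = 21.7. Only an observed effect of about 17 to 21 or 22 points could therefore lose significance, and only at that extreme.

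**The case against.** **The coding rule leaves little missing.** Read literally, a participant who does not complete both tests scores 0. Someone who stops attending is then non-adherent, not missing. This stands as a limit on size: the truly missing share may be well below 10%. To the extent that exits are coded 0 in the primary analysis and imputed in the sensitivity analysis, the two also make different assumptions and comparing them is informative. But the article provides for missing outcomes and budgets for attrition without saying where the line falls. If every exit is coded 0, nothing is left to impute; if exits stay missing in both analyses, the check varies nothing.

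**Imputation can use more information than the model.** A reader might infer that imputation must return the primary answer plus noise. The article does not support that: the imputation model is unspecified, and baseline variables outside the primary model are available. Using them would weaken the MAR assumption. It would still be a form of MAR.

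**The analysis plan may say more.** A reader might also infer that the trial has no analysis for the case where MAR is doubted. The article is only silent on this, and a plan not shown may fill it. What stands is narrower: the article fixes an analysis, a trigger and a purpose that do not fit together.

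**Harm is not shown.** The documents do not link exits to adherence. A smaller simulation (45 people, exits likelier among less adherent people, 60 replicates, 6 imputations, fixed site effects) gave 24.0 points by likelihood and 24.1 by imputation, so bias is not inevitable. The extremes also require every missing usual-care period to be adherent when the expected rate is 10%, or the reverse pattern. This stands, and it keeps the point modest.

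**Conclusion.** The concern holds in limited form. As stated in the article, the imputation analysis shares the MAR assumption of a likelihood-fitted primary model. Without auxiliary variables, agreement between them is not evidence of robustness to departures from MAR, and nothing is stated for when MAR is doubted.

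If all of the roughly 10% attrition were missing outcomes spread evenly over periods 2 to 4, the 24-point effect would be about 22 points with missing set to non-adherent and about 19 to 30 points at opposite extremes. With fewer truly missing outcomes the range narrows. A reader might infer that the primary analysis is invalid or that the effect could reverse. The figures do not support either: no extreme in the table changes the direction, and at the planned effect none falls below the significance threshold implied by the stated power.

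**What to change.** 1. State which person-periods count as missing and which are coded 0, for example death, moving away or withdrawal as against not attending.
2. Keep the multiple imputation, with the baseline variables already collected (age, sex, medical history, blood results, fibrosis scores) as auxiliaries.
3. Add an analysis that departs from MAR and run it whatever mechanism is assumed. One part sets missing to non-adherent. The other is a delta-adjusted or tipping-point analysis with separate shifts for On-Country and usual-care periods, reporting the effect with its CI over the grid and the point, if any, at which the conclusion changes.

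The cost is wording in the analysis plan and a small amount of extra analysis. No new data are needed. If step 1 leaves very few missing person-periods, step 3 will be short.

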### Secondary outcomes

Secondary endpoints will evaluate the feasibility, acceptability and clinical utility of the On-Country model. The model’s feasibility and acceptability will be assessed through the collaborative analysis of yarning circles conducted with participants and staff. A comprehensive economic analysis will compare the cost-effectiveness of the On-Country model to usual care. Finally, the clinical adequacy of the portable liver ultrasounds will be determined using standardised visualisation scores.

#### Yarning

The analysis for the yarning circles involves Indigenous data analysis rather than qualitative analysis. The data component from yarning is story and our unit of analysis will accordingly be storylines, rather than ‘themes’.^39
46^ Yarning circles will be audio recorded and supplemented by researcher notes taken during the yarns. A ‘listening-in’ process will be used whereby the Indigenous Australian investigators will collectively listen to the audio recordings of the yarning circles. The audio recordings and the transcription of the yarning circles are considered paired data sources. The ‘listening-in’ process facilitates appreciation of the meanings of silences, pauses and Indigenous Australian language use. Listening in also returns data collectors to the time of data collection, and this assists with recall of non-verbal communication and other body language, which then provides greater insight for analysis. A transcript uncoupled from the audio recording is considered to be incomplete data which leaves analysis at risk of being one-dimensional. A collaborative approach to analysis will be undertaken, which allows for different Indigenous Australian interpretations of the data in the early stages of analysis to maintain the accuracy and integrity of Indigenous Australian participant voices. It also provides an opportunity to identify potentially sensitive elements of yarning circles that require appropriate custodianship and should not be transcribed but still can be included in analysis as non-textual data.

#### Economics analysis

Generalised linear mixed models will be used to compare differences in costs between the surveillance and control steps of the trial, using the same fixed and random effects as specified for the outcomes analysis. The primary cost-effectiveness endpoint is the incremental cost per additional eligible individual undergoing surveillance, which will be estimated by dividing the difference in the total costs of surveillance across the surveillance and control steps of the trial by the difference in the surveillance prevalence. To represent parameter uncertainty, non-parametric bootstrapping with replacement will be undertaken to generate 5000 bootstrap replicates of the cost and outcome variables. The results of a recently published modelled economic evaluation of 6-month HCC surveillance will be used to extrapolate the effects of observed effects of the intervention on surveillance. In people with cirrhosis, this study reported that 6-monthly HCC surveillance can increase early-stage diagnoses to up to 81% and reduce HCC mortality by 22%.^47^

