### Phase 3: Liver Monitoring (HCC surveillance)

The liver monitoring phase is a 24-month stepped-wedge RCT to compare two models of HCC surveillance (usual care vs On-Country monitoring) for Indigenous Australians who live in very remote communities. The stepped-wedge RCT design is both justifiable and optimal—relative to a conventional parallel clustered trial—in very remote Indigenous Australian community settings because of the small number of sites and because it does not exclude anyone from access to treatment, which could further exacerbate inequities. All sites will have between 6 months and 18 months of usual care before commencing the On-Country HCC surveillance period at different time intervals, which will continue for 6–18 months depending on randomisation allocation (figure 3).

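### As written, the primary cost-effectiveness ratio divides a difference in total costs by a difference in proportions, which is not the cost per additional person surveyed that it is meant to estimate

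*Protocol article*

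**What the plan says.** The Economics analysis section of the protocol article does three things in sequence.

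- It plans a cost model: "Generalised linear mixed models will be used to compare differences in costs between the surveillance and control steps of the trial". This model is to be fitted "using the same fixed and random effects as specified for the outcomes analysis". Under Primary outcome, those effects are treatment, categorical 6-month time, their interaction, and "random intercepts for site and for participant".
- It names the target: "The primary cost-effectiveness endpoint is the incremental cost per additional eligible individual undergoing surveillance".
- It gives the estimator as a quotient: "the difference in the total costs of surveillance across the surveillance and control steps of the trial by the difference in the surveillance prevalence".

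The Data analysis section defines adherence as a proportion of participants. The Primary outcome section records it as 0 or 1 for each participant in each 6-month period. The surveillance prevalence in the denominator is therefore a per-period proportion.

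On exposure, the Phase 3 section gives each site 6 to 18 months of usual care and then On-Country surveillance, "which will continue for 6–18 months depending on randomisation allocation". The Randomisation section puts the switches at 6-month points. The layout itself is in Figure 3, which is not shown.

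**The concern.** A cost per additional person surveyed needs numerator and denominator on the same footing, either both per participant-period or both as totals over the same exposure. The ratio sentence sets a total, accumulated across trial steps, against a proportion. Taken at its word, this has two consequences.

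1. **Scale.** The ratio grows with the number of participant-periods, so recruiting more people raises the apparent cost per person surveyed although nothing about either model of care has changed.
2. **Exposure.** Four sites share three possible switch times, so the two conditions need not cover the same number of site-periods. A condition that runs longer accumulates more cost for that reason alone.

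This is the primary economic endpoint, and the Dissemination and Translation section says that findings will go to federal and state policymakers. The ratio should have only one possible reading.

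**Working it through.** The protocol article states no cost or ratio to reproduce, so the check compares definitions.

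**Inputs from the protocol article**
- 4 sites, 10 participants per site, 4 six-month periods; adherence 10% v 34%, a difference of 0.24 (Sample size and power calculations).
- 1 to 3 control periods per site (Phase 3 section).

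**Assumed inputs.** No unit costs are given. The costs per participant-period below are illustrations only.

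**Possible layouts.** There are 4 × 4 = 16 site-periods. If all three switch times are used, two sites share one. Control periods by site are then (1,1,2,3) = 7, (1,2,2,3) = 8 or (1,2,3,3) = 9, leaving 9, 8 or 7 On-Country site-periods. Multiplying by 10 gives participant-periods M0 (control) and M1 (On-Country).

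**Formulas**, with c = mean cost per participant-period and p = adherence:
- Per-period ratio: (c1 − c0)/(p1 − p0)
- Literal ratio: (M1·c1 − M0·c0)/(p1 − p0)

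**Step 1: scale.** With M1 = M0 = M, the literal ratio is M times the per-period ratio for any costs. At 8:8, M = 80, so the inflation is 80-fold. With the 45 planned recruits, 45/4 = 11.25 per site, M = 8 × 11.25 = 90, and it is 90-fold.

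**Step 2: exposure.** The total-cost difference splits exactly as

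M1·c1 − M0·c0 = [(M1 + M0)/2]·(c1 − c0) + (M1 − M0)·[(c1 + c0)/2].

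The second term comes only from unequal exposure. With assumed costs of 500 (usual care) and 800 (On-Country), the per-period ratio is 300/0.24 = 1,250 in every layout. The literal ratio is:

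| On-Country v control participant-periods | Total-cost difference | Literal ratio | Multiple of 1,250 |
|---|---|---|---|
| 90 v 70 | 72,000 − 35,000 = 37,000 | 154,167 | 123 |
| 80 v 80 | 64,000 − 40,000 = 24,000 | 100,000 | 80 |
| 70 v 90 | 56,000 − 45,000 = 11,000 | 45,833 | 37 |

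In the first row the split is 80 × 300 + 20 × 650 = 24,000 + 13,000. In the last it is 24,000 − 13,000.

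Other assumed costs show the range:
- 200 v 500 (same per-period ratio of 1,250): 129,167, 100,000 and 70,833 in the same row order, or 103, 80 and 57 times too large.
- 500 v 500 (per-period ratio 0): +41,667, 0 and −41,667. The layout alone sets the sign.
- 500 v 550 at 70 v 90: 38,500 − 45,000 = −6,500. The dearer model appears cost-saving.

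**Step 3: are per-participant totals enough?** Suppose the numerator is each participant's total across the steps in a condition.
- At 8:8 each participant has on average 2 periods in each condition. With 500 v 800 the ratio is (1,600 − 1,000)/0.24 = 2,500, twice the per-period value.
- At 9 On-Country to 7 control site-periods, the averages are 9/4 = 2.25 and 7/4 = 1.75 periods. With equal costs of 500 the ratio is (1,125 − 875)/0.24 = 1,042, where the per-period value is 0.

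A per-participant total removes the factor for the number of people but keeps the mixing of exposure time with cost.

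**Step 4: are counts in the denominator enough?** Using (M1·c1 − M0·c0)/(M1·p1 − M0·p0) with 200 v 500:
- 90 v 70: 31,000/(30.6 − 7.0) = 1,314
- 80 v 80: 24,000/(27.2 − 8.0) = 1,250
- 70 v 90: 17,000/(23.8 − 9.0) = 1,149

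This is right only when exposure is equal.

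**The case against.** The strongest reply is that the ratio sentence should not be read alone. The sentence opening the same paragraph specifies a cost model with a participant intercept and period effects. Such a model needs participant-period cost records and yields a period-adjusted difference, which is the natural numerator. Total costs may also simply mean all cost components added together, for example service costs, costs borne by participants and costs from Services Australia data. The endpoint is named per individual, and the bootstrap of cost and outcome variables also suggests individual-level data. On that reading the ratio is (c1 − c0)/(p1 − p0) and does not depend on the layout.

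Much of this stands. The aggregate reading is the literal one but not the only one. A reader might infer that the trial will report a ratio wrong by one to two orders of magnitude, or that raw totals without period adjustment are planned. The document supports neither: it never mentions raw totals, and an analyst who follows the model sentence would not obtain the inflated figures.

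The exposure argument is conditional too. A reader might infer that the switch schedule will bias the ratio or make On-Country care look cost-saving. The layout is in a figure that is not shown and may be 8:8, in which case unequal exposure disappears. The false saving above needs the literal reading, a particular layout and an assumed pair of costs all at once.

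Two things do not stand. The ratio sentence never says that its numerator is the model estimate. And the favourable reading rescues the ratio only if costs are per participant-period, which the text does not say; it speaks of totals across steps, and Step 3 shows that per-participant totals still carry exposure time.

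**Conclusion.** The point holds as a defect in the stated formula, not as proof that the intended analysis is wrong. Read literally, the formula does not estimate the endpoint it is attached to. It overstates the cost per additional participant surveyed in a 6-month period 80-fold with 10 people per site and an 8:8 split, and that factor does not depend on unit costs. If the split is 7:9 or 9:7, exposure time also enters the cost difference; the size and sign of the resulting error then depend on unit costs that the document does not give. Even per-participant totals would double the ratio at 8:8.

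These results rest on 10 participants per site with complete follow-up, the planning difference of 0.24, all three switch times being used and, outside the 8:8 multiples, illustrative costs. If the numerator is in fact the period-adjusted mean cost difference per participant-period, the ratio is sound and only the wording needs repair.

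**What to change.** Replace the ratio sentence in the Economics analysis section with a definition that fixes four things:

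1. **Numerator:** the model-based, period-adjusted difference in mean cost per participant-period, On-Country minus usual care, from the cost model already planned. The borrowed fixed effects include a time-by-treatment term, so state the marginal contrast that supplies this single difference.
2. **Denominator:** the adjusted difference in adherence proportion over the same participant-periods.
3. **Unit:** cost per additional participant surveyed per 6-month period.
4. **Bootstrap:** recompute both adjusted quantities in each of the 5000 replicates.

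The wording should also say that total cost means the sum of cost components within a participant-period, if that is the intention. The cost is rewording only: the same data and models serve, and the extra analysis is negligible.
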